**Immune response**

Current screening methods for evaluating vaccines rely heavily on serologic responses. It could be shown by McElhaney et al. that in adults aged 60 years and older pre- and postvaccination antibody titers after influenza vaccination did not distinguish between subjects who would subsequently develop influenza illness and those who would not (non-LDI-subjects). In contrast, PBMC restimulated ex vivo with live influenza virus preperations showed statistically significant differences between LDI and non-LDI subjects. The mean INFgamma:IL10 ratio in influenza stimulated PBMC was 10-fold lower in LDI vs. non-LDI subjects. The lower ratio in LDI subjects reflects a shift toward a TH2 response and is a potential marker of continued risk of influenzas despite vaccination.

Cellular immunity has rarely been tested in context with infectious agents and vaccination studies. Recent assays for measuring human cellular immunity in clinical trials, eg. INFgammaELIspot assay, and intracellular cytokine measurement by flow cytometry have significantly increased the feasibility to study T-cell responses in clinical trials. (Lindemann, Knutson, Avetisyan)

Kamboj et al. used ELISPOT analysis to measure memory T cell cytokine production after vaccination of adults with conjugated Hib-CRM197 Hemophilus influenzae vaccination. Hib-CRM197 induced a substantial increase in both Th1 (IL2 and IFN-gamma) and Th2 (IL5 and IL10) secreting T cells.

In another publication Kamboj et al showed that immunization with the PCV7 induces a mixed Th1/Th2 CD4+ T cell cytokine response. Immunization with the PCV7 yielded an increase in PBMCs that secreted IL2, IL4, IL5, IL6, IL10 and INF-gamma within 7 days after immunization. The cytokines produced were a direct result of recall responses by carrier portein-specific T cells after reexposure to carrier protein because only CRM197 not polysaccharide or control protein induced T-cell response. In contrast, PBMCs from control subjects immunized with PPV23 produced only small quantities of IL6. This T cell memory may enhance protection induced by vaccines.

Although the reasons for improved effect of conjugate vaccine are not entirely understood, the T lymphocytes activated by the carrier components and the cytokines secreted by them play an important role in the immune response. (Guttormsen). There are different methods to detect an antigen specific T call mediated immune response. Tassignon J et al compared 4 different methods: ELISA, ELISPOT, intracytoplasmic detection and realtime RT-PCR to measure INF-gamma production of PBMCs before and after recall vaccination. In the present study we will use intracytoplasmatic detection of cytokines to define the cellular immune response.

The majority of publications, however, used serum antibody concentrations for defining protection. The pneumococcal IgG antibody assay used clinically for evaluating vaccine responses and the need for revaccination employs routineously the 23-valent polysaccharide vaccine as an antigen in the ELISA, thus measuring levels of IgG to all 23 serotypes included in the polysaccharide vaccine. The new pneumococcal serotype specific IgG assay as we will use in the present study, however, allows to determine the immune response to each single serotype and will provide important additional information regarding the protective status of an individual.

A recent consensus conference by the WHO recommends pneumococcal antibody concentrations of > 0.35 µg/ml as a surrogate for conjugate vaccine efficacy against invasive disease in general (<http://www.who.int/biologicals/Guidelines/vaccines.html>). This threshold level is only reliable after vaccination with the PCV7 where memory cells are induced. Thus, the estimation of seroprotection after vaccination with PPV23 is even more difficult: In contrast to PCV7, PPV23 does not prime the immune system for a rapid booster response. Therefore Sanders defined antibody titers of > 1.0 µg/ml for at least five of seven measured serotypes as predictive for a successful immunization after PPV23 vaccination. Since our patients did not respond to single polysaccharide vaccination and seemed to be at an increased risk of pneumococcal infections, we also chose antibody titers > 1.0 µg/ml as correlate of seroprotection.

**Aim of the study**

The aim of this study is to compare the quantitative antibody responses of PPV23 with those of a sequential schedule of PCV7 followed by PPV23 12 months later in adult renal transplant recipients by measuring the concentrations of serotype-specific IgG in sera using an isotype-specific ELISA that has recently been recommended by the World Health Organization.

For a subset of subjects the T-cell mediated immune response will be evaluated in both groups.

**Materials and Methods**

*Study population:*

Adult patients will be recruited at the transplant center of the Medical University of Vienna. It is estimated that 100-200 kidney transplantations take place per year.

Patients will be eligible if between 6 months and 3 years had passed since their kidney transplant and if they have stable allograft function, as evidenced by a creatinine level < 250 µmol/L for 1 month prior involvement.

Basic demographic data including age, gender, and medical history will be obtained.

Exclusion criteria included previous splenectomy, pneumococcal vaccination within the preceding 5 years, ongoing treatment for an episode of allograft rejection, any acute febrile illness in the 2 weeks prior to or at the time of enrolment, and use of intravenous immunoglobulin within preceding 6 month, have a history of severe allergic reactions or anaphylaxis. No changes to the current immunosuppression protocol will be made for the study.

Subjects will be exclude from participation in the evaluation of cellular immunity if they show a haemoglobin value < 10 g/dl.

*Study design and vaccines:*

A randomized, double blind, controlled trial will be performed. Eligible patients will be randomly assigned to receive a single dose of PCV7 (Prevenar; Wyeth Pharma GmbH) or PPV23 (Pneumo23, Sanofi-Pasteur-MSD, Lyon, France) in the deltoid muscle.

The PCV7 is a 7-valent pneumococcal conjugate vaccine containing 2µg polysaccharides of the serotypes 4, 14, 9V, 18C, 19F, 23F, respectively and 4 µg of the serotype 6B in 0.5 ml. The polysaccarides are conjugated to the carrier protein CRM197 and adsorbed to aluminum phosphate. PCV7 induces T cell dependent immune response that results in protective levels of antibody in infancy, as well as inducing booster response with subsequent doses.

The PPV23 is a polysaccharide vaccine containing 25 µg of 23 pneumococcal serotypes: 1–5, 6B, 7F, 8, 9N, 9V, 10A, 11A, 12F, 14, 15B, 17F, 18C, 19A, 19F, 22F, 23F, and 33F in 0.5 ml. This vaccine contains the individually extracted and purified capsular polysaccharides, which are combined into the final vaccine product. Polysaccharide vaccines are indicated for use in adults and children age > years who are at high risk for pneumococcal disease.

Participants will be enrolled into the study by the principal investigator. The vaccine will be assigned from a computer-generated randomization schedule, immediately before administration.

The administrator of the vaccine and the patient will be blinded to the type of vaccine given.

Patients randomized to group A will receive the PPV23 vaccine as early as 6 months after transplantation and the second dose of PPV23 12 months after the first vaccination.

Patients randomized to group B will receive the first PCV7 as early as 6 months after transplantation, followed by a PPV23 dose 12 months after the PCV7.

|  | 6 M after Tx | 18 M after Tx |
| --- | --- | --- |
| Regime 1 | PPV23 | PPV23 |
| Regime 2 | PCV7 | PPV23 |

*Study endpoints:*

Immunogenicity:

- Antibody concentrations after vaccination
- Fold increase of antibody response as compared to baseline 8 weeks after the vaccination
- Number of subjects with seroconversion defined as minimum 2-fold titer increase and a serum concentration of at least 1 µg/ml
- Number of subjects with at least > 2-fold increase for 2 of the 7 measured serotypes

For the subset of subjects included in the evaluation of cellular immunity

- T-cell response after each vaccination as determined by the frequency of cytokine producing T-cells induced by conjugated pneumococcal Ag
- Increase in frequency of cytokine producing T-cells induced by conjugated pneumococcal Ag after each vaccination as compared to baseline

*Safety data:*

Patients will be instructed to record local reactions /e.g. redness, swelling, and tenderness) and systemic reactions (e.g. fever, nausea, and vomiting).

At the time of vaccination, medical providers will be asked to record appearance of local reactions occurring within 30 minutes of injection. At the time of each vaccination visit patients will be given a diary card, thermometer and a measuring tape. On postvaccination days 1 through 3 patients will be asked to record presence or absence of redness and swelling (in millimetres), pain/tenderness (graded none, mild, moderate or severe), loss of appetite, vomiting, headache, fussiness, increased sleep or other potential adverse reactions. Data from the diary will be recorded as well as changes in medications or medical care.

Serum samples will be obtained immediately before, 8 weeks the first and the second vaccination.

In a subgroup of patients in each treatment regimen blood for cellular response will be taken immediately before vaccination and 7-10 days after vaccinations.

*Definitions and statistical methods:*

All patients will be included in the analysis as randomised.

Although the primary endpoint is the difference in antibody concentration as continuous variable between study groups we base our sample size calculation on the more conservative but clinically more useful binary variable vaccine response. A vaccine response by ELISA will be defined as a > 2 fold increase in prevaccination titer and an absolute postvaccination value of at least 1 µg/ml.

The study is powered to detect an improvement in vaccine response with the conjugate vaccine in any of the 7 serotypes. The study is set to yield a power of 80% at a significance level of 5% to detect a 35% improvement in the response rate for a given serotype. The response rate in the control group is expected at about 45%. Thus the calculated sample size will be 35 in each group. We added 10% to adjust for potential loss-to-follow-up which results in 39 patients in each group.

We expect antibodies being log-normally distributed. Geometric mean antibody concentrations (GMCs) for each pneumococcal serotype will be compared between the two groups by using the 2-tailed, unpaired Students’s t-test after log transformation of the raw data, given our distributional assumptions hold.

For binary variables we will calculate risk ratios and exact 95% confidence intervals. Vaccination efficacy (Ev) will be calculated as: Ev = (1-RR) x 100. For hypothesis testing we will use the Fisher’s exact test.

All analysis will be conducted by using a 2-sided p value with a type I error rate of < 0.05.

*Determination of serum antibodies against vaccination antigens:*

Serum IgG antibodies against the seven pneumococcal conjugate polysaccharides included inthe heptavalent vaccine were measured by enzyme-linked immunosorbent assays (ELISA). Serotype-specific IgG antibody concentrations to pneumococcal serotypes 4, 6B, 9V, 14, 18C, 19F and 23F were measured by reference ELISA according to the WHO protocol and to the publication of Wernette et al. [14, 15]. Briefly, 96-well microtiter plates (Greiner, Germany) were coated with previously determined optimal antigen concentrations (1 g/ml for serotype 14; 2 µg/ml for serotypes 4, 9V, 18C and 5 g/ml for serotypes 6B, 19F and 23F) and incubated at 37°C for 5 h in a humidified chamber. The coated plates were stored at 4°C and used within three weeks. Standard reference serum (89SF), kindly provided by [name] (Center for Biologics Evaluation and Research, U.S. Food and Drug Administration, Rockville, MD, USA), was used for assay standardization and was absorbed with 5 g/ml of highly purified cell-wall polysaccharide (C-Ps) (Statens Serum Institute, Copenhagen, Denmark). Quality controls (QC) and serum test specimens were preincubated with 5 g/ml C-Ps as well as pneumococcal serotype 22F capsular polysaccharide at a final concentration of 10 g/ml to remove cross-reactive antibodies [16].

The coated plates were washed five times with 1 x Tris-buffered saline (TBS) containing 0.1% BRIJ35 (pH 7.2), then serially diluted 89SF, QC and serum samples were added in duplicate to the plates and incubated for 2 h at room temperature. Plates were washed again as described above and 50 l of 1:5000 diluted goat anti-human IgG-alkaline phosphatase conjugate (Sigma) was added to each well. After incubation for 2 h at room temperature and a final washing step the plates were developed with 100 l of nitrophenyl-phosphate substrate (Sigma) (1 mg/ml) for 30 min at room temperature. The enzyme reaction was stopped with 50 l of 3M NaOH and the absorbance was measured at wavelength 405 nm in an ELISA reader. Concentrations of pneumococcal IgG antibody were calculated with a weighted log-logit computer program. The interassay coefficient of variation was about 20%.

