# **Scientific/Medical section**

**Introduction:**

Although many of the diseases that routine immunization prevents are rare in solid organ transplant recipients, there are several important reasons to ensure that these patients remain up to date on their immunizations. First, while antibody titers achievable in transplant candidates are often suboptimal as a result of immunosuppression associated with the underlying liver or renal failure, antibody responses are usually even worse when vaccines are administered after transplantation. Second, the safety of immunization with living virus vaccine such as MMR and varicella is not established, so that these vaccines are contraindicated in transplant recipients receiving exogenous immunosuppression. Third, many transplant recipients are not immunized after transplantation because of concerns about allograft rejection triggered by immunization.

The challenges to immunize solid organ transplant candidates include unpredictable waiting times, requiring accelerated schedules of vaccine administration in some patients while others wait for prolonged periods and require regular re-evaluation of their immunization status.

For tetanus and diphtheria we evaluated the immune status in patients with chronic heart failure and after heart transplantation. As seen in the figure the immunisation rate for diphtheria (% of patients with serum concentrations above the so called protective value) is poor and revaccination should be performed in both groups of patients. Tetanus vaccine is a vaccination which is used frequently in Austria, therefore adequate antibody titers are even found in such “risk patients”.

Solid organ transplant recipients usually receive lifelong immunosuppression. No formal recommendations have been developed about when to resume immunizations but many transplant centers withhold immunizations until the patients is taking baseline immunosuppression. In some centers, all immunizations are withheld during the first transplant year. In the present study we will start with immunization at least 6 months after transplantation.

In addition, immunosuppressive therapy is being improved continually and in most cases little is known about the impact of the more recently adopted regimens on durability of antibody response. Thus studies on immune-response after vaccination in patients with different immunosuppressive regimes are still missing.

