However, the use of immunsuppressive medications such as cyclosporine, prednisone, tacrolimus and mycophenolate mofetil may impair these patients response to vaccination. Studies that assessed the immunogenicity of polysaccharide vaccine in renal transplantation have demonstrated variable protective efficacy but, collectively, have produced suboptimal responses when functional antibody responses have been assessed. One way to overcome this problem is the development of more effective vaccines.

Recently, conjugate pneumococcal vaccines have been developed, whereby the immunogenicity of capsular polysaccharides is enhanced by covalent conjugation with carrier proteins. The currently available conjugate pneumococcal vaccine (PCV7) contains 7 capsular polysaccharides (serotype 4, 6B, 9V, 14, 18C, 19F and 23F).

The efficacy of the conjugate vaccine is due to several mechanisms: increased amounts of circulating antibodies, higher avidity, and an induction of immunological memory. (Ahmed, Eskola-Antilla, Jodar, Chan,)

PCV7 elicits a T-cell dependent response, which, in turn, induces the T helper cell to stimulate polysaccharide-specific B cells to mature into either antibody-producing plasma cells or memory cells (Eskola J, Stein). The creation of this immunologic memory may be crucial in immunocompromised organ transplant recipients, in whom immunity to pneumococcus wanes quickly after polysaccharide vaccination. (Linnemann, First).

In a randomized trial comparing PPV23 to PCV7 in adult kidney transplant recipients, it could be demonstrated that the conjugate vaccine is immunogenic in this population. However, there was no significant difference in immunogenicity demonstrated between the two vaccines at 8 weeks postvaccination.

It could also be shown that the conjugate vaccine does not lead to a more durable antibody response for any of the 7-serotypes covered in this vaccine when compared to polysaccharide vaccine. Overall response rates were generally suboptimal for both groups, but this could potentially be overcome with repeat dosing schedules or higher doses of vaccine.

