**Schedule of events**

| **Procedure/assessment** | **Visit 1** | **Visit 1a**  **Day 7** | **Visit 2**  **Day 56** | **Visit 3**  **Day 365** | **Visit 3**  **Day 372** | **Visit 4**  **Day 421** |
| --- | --- | --- | --- | --- | --- | --- |
| Informed Consent | X |  |  |  |  |  |
| Inclusion/Exclusion Criteria | X |  |  |  |  |  |
| Medical History | X |  |  |  |  |  |
| Physical Examination | X |  |  |  |  |  |
| Blood Draw (Serology) | X |  | X | X |  | X |
| Blood Draw (Cellular Immunity) | X | X |  | X | X |  |
| Vaccination | X |  |  | X |  |  |
| Subject Diary (Part 1) | X |  | R |  |  |  |
| Subject Diary (Part 2) |  |  |  | X |  | R |
| AE Assessment | X | X | X |  | X | X |
|  |  |  |  |  |  |  |

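### Immunosuppression is named as a likely cause of poor vaccine response, but the protocol does not specify that the baseline regimen be recorded, schedules no medication check at dose 2, and fixes an unadjusted primary comparison

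*Protocol*

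**What the plan says.** All references are to the protocol.

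- **Why the regimen matters.** The Introduction, like the synopsis Background, states that drugs including "tacrolimus and mycophenolate mofetil may impair these patients response to vaccination". It also notes: "Thus studies on immune-response after vaccination in patients with different immunosuppressive regimes are still missing".
- **Baseline data.** Materials and Methods, Study population: "Basic demographic data including age, gender, and medical history will be obtained". The work packages under Time table and time schedule add blood counts, antibodies and cellular immunity, but not the regimen.
- **Treatment during the study.** The same section says: "No changes to the current immunosuppression protocol will be made for the study".
- **Changes.** Under Safety data: "Data from the diary will be recorded as well as changes in medications or medical care". This follows the description of the reaction diary, which begins: "On postvaccination days 1 through 3 patients will be asked to record presence or absence of redness and swelling".
- **Schedule of events.** There are six columns: Visit 1 and Days 7, 56, 365, 372 and 421. Medical history appears at Visit 1 only. No row covers medication. Dose 2 is given at Day 365, where there is no adverse-event assessment either. No visit falls between Days 56 and 365.
- **Analysis.** Definitions and statistical methods fixes a two-sided unpaired t-test on log concentrations for each serotype and Fisher's exact test for binary variables. No covariate is named there, and no stratification factor is named where randomisation is described.

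**The concern.** The protocol identifies a likely determinant of its own primary endpoint but does not say that it must be written down. A statistical analysis plan can set covariates and tables, but it can use only what the protocol causes to be collected.

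Three things are at stake. Without a specified baseline record, the report may be unable to show that the arms were alike on this factor. Readers could not tell which regimens the results apply to. Precision that adjustment could give in a trial of 39 per arm is forgone.

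Dose 1 is given as early as 6 months after transplantation and dose 2 comes 12 months later. The undertaking not to alter immunosuppression for the study does not exclude routine clinical changes in that interval, and no scheduled check would document them.

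**Working it through.** **1. The plan's own figures.** 45% against 80% response, two-sided 5%, 80% power and a continuity correction give 35 per arm. Allowing 10% loss, 35/0.9 = 38.9, so 39 per arm and 78 in total. Both reproduce, and nothing below changes them.

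**2. Assumptions.** The documents give no regimen prevalence, no regimen effect and no SD of log concentration. I assume that:
- half of the 78 patients (39) take a given agent;
- the agent divides the geometric mean concentration (GMC) by f = 2 (range 1.5 to 3);
- the total SD on the log10 scale is 0.5.

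**3. Chance imbalance.** With 39 of 78 exposed and 39 per arm, the number exposed in one arm is hypergeometric with variance 39 × 0.5 × 0.5 × 39/77 = 4.94, so SD 2.22. The between-arm difference in share has SD 2 × 2.22/39 = 0.114, or 11.4 points.
- P(difference of at least 15 points) = 17.4%
- P(difference of at least 20 points) = 6.9%

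Treating the arms as independent binomial samples, with prevalence from 20% to 50%, gives 32% to 43% for at least 10 points and 3% to 9% for at least 20 points.

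**4. What an imbalance does to the estimate.** A 15-point imbalance moves the GMC ratio by f^0.15: 1.06 for f = 1.5, 1.11 for f = 2 and 1.18 for f = 3. The standard error of the log10 GMC ratio is 0.5 × √(2/39) = 0.113, so the 95% limits already lie a factor of 10^(1.96 × 0.113) = 1.67 either side. The central shift is 0.15 × 0.301/0.113 = 0.4 standard errors.

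**5. Precision available from adjustment.** The variance explained by a binary factor at 50% prevalence is R² = 0.25 × (log10 f)²/0.5², which equals (log10 f)². The standard error is multiplied by √(1 − R²).

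| f | R² | Reduction in SE |
|---|---|---|
| 1.5 | 3% | 1.6% |
| 2 | 9% | 4.6% |
| 3 | 23% | 12% |

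**6. Price of the extra terms.** With two added terms (a binary regimen class and age) and 78 patients, chance correlation with arm inflates the variance by about (78 − 3)/(78 − 2 − 3) = 75/73 = 1.027, and the standard error by about 1.4%. At the low end of the range this nearly cancels the gain. In the central case about 3% remains: 0.954 × 1.014 = 0.967. Any contribution from age is not counted.

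**The case against.** Several points on the other side are sound.

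- **The regimen is not wholly ignored.** A reader might infer that no visit records it and that a change between doses must go unseen. The documents do not support that. The Safety data text provides for recording changes in medications, with no explicit limit to days 1 to 3. Medical history at Visit 1 may cover current drugs, and the baseline list is introduced as non-exhaustive. At a single transplant centre the information should also be in the clinic chart. What remains is that the starting regimen is not specified as a study item and that no visit is assigned a check.
- **No stated objective fails.** A reader might infer that the trial promised a comparison of regimens. The lack of such studies is background. The Aim compares two vaccine schedules.
- **The test is valid.** Under randomisation, a chance imbalance is part of the random error that the t-test already allows for. The loss is in precision and documentation.
- **Covariates often belong in the analysis plan,** which is not shown here. That is a fair limit on the modelling part. It does not reach data capture, and the protocol does fix a specific unadjusted test for its primary endpoint.
- **The protocol's age data are weak support.** Its table of responses below two-fold gives 89/147 = 60.5% over age 60 and 109/217 = 50.2% under 60, pooled over serotypes. Those patients were not transplant recipients: they were asplenic, with haematological malignancy or trauma. Pooling also counts each of the 21 and 31 patients seven times. The largest gap, serotype 23F (61.9% against 35.5%), gives Fisher p = 0.09. Age is a sensible covariate because it is already collected, not because this table proves its effect.

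**Conclusion.** The point holds as a cheap improvement to data capture and to the model. It is not a flaw that invalidates the comparison. The protocol names immunosuppression as likely to impair response, does not specify that the baseline regimen be recorded, and schedules no medication check at dose 2 or between Days 56 and 365.

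The expected gain is modest: a standard error about 5% smaller if regimen explains 9% of the variance, or 2% to 12% smaller for 3% to 23%, less roughly 1.4% for two extra terms. These figures rest on assumed prevalence, effect and SD. The gain in documented comparability does not depend on them.

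A reader might also infer that the analysis should adjust for the regimen in use at each dose. That does not follow. The regimen at dose 2 is observed 12 months after randomisation, and the protocol's own background cites concern that immunisation may trigger rejection. It could therefore be affected by arm, and adjusting for it could bias the comparison after dose 2.

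**What to change.** 1. **Record it.** Add immunosuppression (drug, dose, last available level, taken from the clinic chart) to the baseline list under Study population. Add a matching row to the Schedule of events at Visit 1, with an update at Days 56, 365 and 421.
2. **Adjust for baseline values only.** In Definitions and statistical methods, replace the t-test on log concentrations with a linear model on log concentration containing arm, regimen class at Visit 1 and age. Fix the regimen classes before unblinding, and use pre-randomisation values only.
3. **Describe the rest.** Report the regimen at dose 2 by arm, without adjusting for it.

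**Cost:** one case-report-form entry at each of four visits, one classification to agree and a few model degrees of freedom. Few classes should be used, because each extra term erodes a small gain. No extra visit, blood sample or patient is needed, no treatment changes, and the sample size stays at 39 per arm.

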The study is powered to detect an improvement in vaccine response with the conjugate vaccine in any of the 7 serotypes. The study is set to yield a power of 80% at a significance level of 5% to detect a 35% improvement in the response rate for a given serotype. The response rate in the control group is expected at about 45%. Thus the calculated sample size will be 35 in each group. We added 10% to adjust for potential loss-to-follow-up which results in 39 patients in each group.

We expect antibodies being log-normally distributed. Geometric mean antibody concentrations (GMCs) for each pneumococcal serotype will be compared between the two groups by using the 2-tailed, unpaired Students’s t-test after log transformation of the raw data, given our distributional assumptions hold.

For binary variables we will calculate risk ratios and exact 95% confidence intervals. Vaccination efficacy (Ev) will be calculated as: Ev = (1-RR) x 100. For hypothesis testing we will use the Fisher’s exact test.

All analysis will be conducted by using a 2-sided p value with a type I error rate of < 0.05.

**Safety precautions:** Patients will be instructed to record local reactions /e.g. redness, swelling, and tenderness) and systemic reactions (e.g. fever, nausea, and vomiting).

At the time of vaccination, medical providers will be asked to record appearance of local reactions occurring within 30 minutes of injection. At the time of each vaccination visit patients will be given a diary card, thermometer and a measuring tape. On postvaccination days 1 through 3 patients will be asked to record presence or absence of redness and swelling (in millimetres), pain/tenderness (graded none, mild, moderate or severe), loss of appetite, vomiting, headache, fussiness, increased sleep or other potential adverse reactions. Data from the diary will be recorded as well as changes in medications or medical care.

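### The diary item list omits fever and nausea although patients are told to record them, and systemic reactions on the vaccination day have no systematic record, most clearly at the second dose

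*Protocol*

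**What the plan says.** The rules for collecting reactions stand in the Protocol under Materials and Methods (Safety data) and are repeated in the Study synopsis (Safety precautions).

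- A general instruction asks patients to record local reactions and "systemic reactions (e.g. fever, nausea, and vomiting").
- On site, "medical providers will be asked to record appearance of local reactions occurring within 30 minutes of injection".
- Equipment: "At the time of each vaccination visit patients will be given a diary card, thermometer and a measuring tape".
- Diary window and first items: "On postvaccination days 1 through 3 patients will be asked to record presence or absence of redness and swelling (in millimetres"). Graded pain or tenderness comes next, and the list ends with "loss of appetite, vomiting, headache, fussiness, increased sleep or other potential adverse reactions".

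The Schedule of events adds two relevant rows. Vaccination is marked at Visit 1 and Day 365: "Vaccination | X | | | X". The adverse event row, whose columns are Visit 1, Day 7, Day 56, Day 365, Day 372 and Day 421, reads "AE Assessment | X | X | X | | X | X". It is empty at Day 365. The two diary parts are handed out at the vaccination visits and returned at Day 56 and Day 421.

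The Day 7 and Day 372 columns hold only the blood draw for cellular immunity and the AE assessment. Of that draw, Materials and Methods says: "In a subgroup of patients in each treatment regimen blood for cellular response will be taken immediately before vaccination and 7-10 days after vaccinations".

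**The concern.** Two statements in one section do not match. The general instruction puts fever first among systemic reactions, and a thermometer is supplied, but the list to be completed each day has nowhere named for the reading. Nausea is missing as well. Fussiness, an item suited to infants, is on the list in a trial of adults, which suggests that the list was not adapted to this population.

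Timing adds to this. The provider's record is confined to local reactions, although the eligibility criteria in Materials and Methods treat a history of severe allergic reaction or anaphylaxis as a reason for exclusion. The diary then appears to begin the next day.

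The completeness of the reaction data at both doses is at stake. A prompted daily item separates a reaction that did not occur from one that nobody wrote down, and an open field does not. What is not solicited at the time cannot be recovered in the analysis.

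**Working it through.** The plan states no figure to reproduce here. The check sets the passages side by side and uses simple day arithmetic.

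**Step 1: items.** The general instruction against the itemised diary list:

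| Reaction | General instruction | Diary list |
|---|---|---|
| Redness, swelling, tenderness | named | named |
| Vomiting | named | named |
| Fever or temperature | named | not named |
| Nausea | named | not named |
| Loss of appetite, headache, fussiness, increased sleep | not named | named |

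Of the three systemic examples in the instruction, one (vomiting) has a line and 3 − 1 = 2 have none. Those two can still be entered under the closing open item.

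**Step 2: what day 1 means.** Inputs are the visit days in the Schedule of events and the serum sample planned 8 weeks after each vaccination.

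- After dose 1: 8 × 7 = 56, which matches Day 56.
- After dose 2, given on Day 365: 421 − 365 = 56 and 372 − 365 = 7.

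The schedule thus counts elapsed days from the injection, with the vaccination day as day 0. On that count, day 1 after vaccination is the following day. This is an inference: Visit 1 carries no day number, and the diary's own day convention is not defined. If the vaccination day were day 1, the first-evening gap would close and the diary would end one day sooner.

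**Step 3: cover over time, on the day-0 reading.**

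| Period | Dose 1 | Dose 2 |
|---|---|---|
| 0 to 30 minutes | provider record, local only; AE assessment at Visit 1 | provider record, local only; no AE assessment marked |
| 30 minutes to end of vaccination day | general instruction only | general instruction only |
| Days 1 to 3 | diary list, without fever or nausea lines | same |
| About 7 days | AE assessment at Day 7 | AE assessment at Day 372 |
| 8 weeks | AE assessment and diary return at Day 56 | AE assessment and diary return at Day 421 |

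**Step 4: who attends at about 7 days.** The only other procedure at those visits is the cellular-immunity draw, which is planned for a subgroup. The schedule does not say whether other patients attend. If they do not, their next AE assessment comes 56 days after the dose, when recall of a short fever or of nausea is a poor substitute for a daily entry.

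**Step 5: size.** The protocol gives no expected reaction rates, so the number of reactions missed cannot be computed.

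**The case against.** The strongest reply is that fever and nausea are in fact requested. The instruction names them without a day limit, the thermometer shows that temperature is meant to be taken, and the list ends with an open item. The printed diary card is not among the documents and may hold a temperature line. This stands to the extent that neither reaction is excluded. It does not remove the mismatch, because the protocol text is what fixes the items to be solicited.

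Second, AE assessments are scheduled, and the one at Visit 1 is not limited to local reactions. That stands for dose 1. It does not help on the day of dose 2, where the row is empty.

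Third, the stakes are limited. Every listed endpoint is immunological, no hypothesis on reaction rates is stated, and both arms use the same diary with patient and vaccine administrator blinded. All of this stands.

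Three stronger readings are tempting, and the documents support none of them:

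- A reader might infer that early and febrile reactions are under-counted. The text shows only that they may be captured incompletely.
- A reader might infer that the first evening is lost from every count. A reaction still present the next day falls inside the diary window, and one that has resolved can still be reported under the general instruction or at an AE assessment. An injection at 10:00, an assumed time, would leave 13.5 hours (10:30 to midnight) without a prompted entry, but clock hours are not missed reactions.
- A reader might infer that the arms cannot be compared on fever. Fever can be analysed as a binary variable with the risk ratios and Fisher's exact test that the protocol names. The doubt concerns how completely it is recorded. Nor is the lack of a grade peculiar to fever, since only pain or tenderness has a stated severity scale.

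**Conclusion.** The point holds as a gap in systematic capture that should be corrected. Two of the three systemic reactions named to patients have no line in the itemised list. The 30-minute record is worded as local only. On the most natural reading, the rest of the vaccination day has no prompted entry. The weakest place is dose 2, where no AE assessment is marked on the day of injection.

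Two assumptions carry part of this: that the diary counts days as the visit schedule does, and, for the longer wait until the next AE assessment, that the Day 7 and Day 372 visits are confined to the cellular-immunity subgroup. The item mismatch, the local-only wording and the empty Day 365 cell need neither assumption.

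The amount of missing information cannot be quantified, and no differential bias between the arms is shown. The primary endpoint and the sample size are not affected.

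**What to change.** Make these changes in both the Study synopsis and Materials and Methods, and in the Schedule of events where it applies:

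1. Reconcile the instruction with the list by adding a daily measured temperature and a nausea line to the diary, and drop fussiness.
2. State that the diary starts on the vaccination day, defined as day 0, and runs through day 3.
3. Extend the provider's 30-minute record to systemic as well as local reactions.
4. Mark AE Assessment at Day 365, and state whether the Day 7 and Day 372 visits apply to all patients or only to the subgroup.

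The cost is small: a slightly longer diary card, with one more daily column and two new lines in place of one removed, and a little more to note at the vaccination visit. Reported reaction rates will probably be somewhat higher because more is asked, and the report should say so.
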